**Principal Investigator: [name], MPH, MA**

1. **SPECIFIC AIM**

Conduct a randomized controlled trial to compare the Fit after Baby program with a mobile texting control group (Text4Baby).

1. **HYPOTHESIS**

Women randomized to the Fit After Baby program will demonstrate greater weight loss and less postpartum weight retention than women randomized to the Text4Baby group.

1. **BACKGROUND AND SIGNIFICANCE**

**A. Pregnancy as a “stress test”:**

Pregnancy complications provide an early warning of future cardiometabolic risk.^[[1]](#endnote-1)^ This harbinger of risk can identify women long before traditional risk factors for cardiovascular disease and diabetes are detected in the primary care setting.^[[2]](#endnote-2)^ Women with pregnancies complicated by gestational diabetes mellitus (GDM) have a ~50% increased risk for developing type 2 diabetes mellitus within 10 years, are likely to develop atherosclerosis earlier,^[[3]](#endnote-3)^ and have increased risk for hypertension^[[4]](#endnote-4)^ and cardiovascular disease (CVD).^[[5]](#endnote-5),^^[[6]](#endnote-6)^ Preeclampsia, preterm delivery, delivery of a small-for-gestational age (SGA) neonate, hypertensive disorders in pregnancy, and GDM are independently associated with a 50-300% increased risk for CVD.^[[7]](#endnote-7)^ About 30% of US women will have at least one of these predictive conditions during pregnancy.^[[8]](#endnote-8)^

**B. Cardiovascular disease and diabetes confer significant mortality in US women**: Cardiovascular disease is the leading cause of death, and diabetes the seventh leading cause of death, among US women. Among women 45-54, the first decade following the childbearing years, CVD and diabetes are the second and seventh leading causes of death, respectively.^[[9]](#endnote-9)^ Given this early risk, in 2011 the American Heart Association recommended taking a history of pregnancy complications when evaluating cardiovascular risk, and included a history of preeclampsia, gestational hypertension, and/or GDM as major risk factors for CVD.^[[10]](#endnote-10)^ The risk factors revealed in pregnancy are exacerbated by overweight, which increases the risk for CVD and diabetes in women at every age and in every ethnic group, by 40% for overweight and by as much as 300-400% for severe obesity.^[[11]](#endnote-11)^ It is currently estimated that 50-60% of U.S. women of childbearing age are overweight or obese.^[[12]](#endnote-12)^ The cost of obesity in the US is considerable, as much as $147 billion annually.^[[13]](#endnote-13)^ Notably, the presence of obesity among women age 45-54 increases the lifetime cost of cardiovascular disease and diabetes by nearly 200%.^[[14]](#endnote-14)^

**C. The postpartum period is a critical window of opportunity**: Studies demonstrate that pregnancy weight retained beyond 6-12 months postpartum is usually retained long-term and is a powerful independent risk factor for future obesity.^16^ Importantly, up to 60% of previously normal weight pregnant women become overweight in pregnancy and the American College of Obstetricians and Gynecologists considers overweight and obesity the leading cause of maternal and neonatal morbidity.^[[15]](#endnote-15),^^[[16]](#endnote-16)^ Given the significance of postpartum weight retention, the postpartum year is considered a critical window of opportunity to make lifestyle changes to decrease future risk of obesity and chronic disease.^14,^^[[17]](#endnote-17),^^[[18]](#endnote-18)^ Lifestyle changes, including weight loss, smoking cessation, improved diet, and physical activity have been shown to decrease risk for diabetes and CVD.^[[19]](#endnote-19),^^[[20]](#endnote-20),^^[[21]](#endnote-21),^^[[22]](#endnote-22),^^[[23]](#endnote-23)^ Reducing postpartum weight retention also decreases risk for weight-related complications in future pregnancies, including GDM, preeclampsia, and perinatal mortality.^[[24]](#endnote-24),^^[[25]](#endnote-25)^ Lifestyle changes made by mothers in the postpartum period have the potential to improve health of other members of the household, including partners and children, thereby broadening the impact. Studies demonstrate that postpartum women may be particularly receptive to making lifestyle changes given their new awareness of risk factors that were unmasked during pregnancy as well as their motivation to create a healthy home for their offspring.^[[26]](#endnote-26)^

**D. A lack of available treatment options:** Despite the importance and critical timing of the postpartum period, there are currently no clinically available evidence-based programs designed for high-risk postpartum women.^[[27]](#endnote-27)^ Few lifestyle intervention studies have been conducted in postpartum women at elevated cardiometabolic risk.^[[28]](#endnote-28)^ Although the Diabetes Prevention Program (DPP) demonstrated successful weight loss and reduction in diabetes incidence in an older population of pre-diabetics,^34^ women in the DPP with a history of GDM lost less weight and were less likely to sustain changes in physical activity than women without a history of GDM.^[[29]](#endnote-29)^ Studies attempting intensive face-to-face methodologies similar to the DPP in postpartum women demonstrate limited efficacy and poor retention.^[[30]](#endnote-30),^^[[31]](#endnote-31),^^[[32]](#endnote-32)^ This is due, at least in part, to multiple barriers to face-to-face participation described by postpartum women, including time constraints, infant and breastfeeding demands, older childcare responsibilities, and reluctance to spend time away from family.^[[33]](#endnote-33),^^[[34]](#endnote-34)^ Given the high stakes for failure in the face of these barriers, there is increasing interest in using technology to improve the efficacy of lifestyle interventions for this high risk population.^33,43^

**3.1 Innovation:**

**A. Target population:** Despite increasing recognition that obstetric history may identify at-risk women before their physiologic markers or cardiovascular risk score may prompt a referral to a specialist, there are no initiatives in primary care that I am aware of to intervene in this high-risk population. Although a few small-scale time-intensive specialty clinics do exist for postpartum women who have had pregnancy complications,^[[35]](#endnote-35)^ feasible, cost-effective, scalable solutions to address cardiometabolic risk at the population level are sorely needed. Given the current high rates of obesity, CVD, diabetes, and prediabetes (recently estimated to be 38% of US adults),^[[36]](#endnote-36)^ this is a timely and potentially transformative approach.

**B. Use of mHealth:** Women of childbearing age are one of the fastest growing user groups for cell phones and smartphones, across race and socioeconomic class.^20^ Leveraging mobile technology for health promotion provides the unprecedented opportunity to communicate and provide support for behavioral choices in “ecological moments;” real-time moments when people make lifestyle decisions. In addition, mHealth technology greatly facilitates tracking of behavior and weight, allowing for real time recording, feedback, and accountability. In light of escalating health care costs and rapid increases in the incidence of cardiometabolic disease, extending the reach of health promotion into daily life is an innovative approach for high-risk women with multiple and intensive family/work demands. An mHealth lifestyle intervention for the population of women at elevated cardiometabolic risk would leverage the widespread adoption of mobile devices among women of reproductive age, and offer the potential of a scalable and cost-effective program that could extend health promotion beyond the traditional clinic visit into home and daily life.

**C. Evidence-based approach integrating behavioral theory:** Although there has been an explosion of use of mobile phones and health-related apps, the vast majority of available apps do not adequately include evidence-based strategies^[[37]](#endnote-37),^^[[38]](#endnote-38)^ or use behavioral theory,^[[39]](#endnote-39),^^[[40]](#endnote-40)^ and almost none have been rigorously tested.^[[41]](#endnote-41)^ To my knowledge, there are no apps specifically designed for postpartum women at elevated cardiometabolic risk. The majority of postpartum apps available commercially are centered around babies, not mothers’ health, and include activities like tracking infant feedings and sleep. I have developed the mHealth *Fit After Baby* program to address this gap. We have developed the app using evidence-based strategies for weight loss, cardiometabolic disease prevention, and behavior change.

**5. METHODS**

**5.1: Rationale:**

This pilot RCT is designed to provide preliminary data to support the design of a larger pragmatic trial for a future R01 proposal to assess weight loss and impact on risk factors in postpartum women at elevated risk for cardiometabolic disease.

**5.2: Source of subjects and recruitment methods:**

The Colorado study staff has completed training in the protection of human research participants (CITI) and will recruit subjects from the University of Colorado and Denver Health patient populations.

At the University of Colorado Hospital, women who are attending clinic visits at the OB/Gyn clinic will be prescreened via medical records and via our existing treatment relationship. All potential women will be approached for recruitment. Women will be consented during their clinic visit in a private exam room by a study physician or by a professional research assistant (PRA). In addition, women who are inpatients at the University of Colorado will be identified through the recruitment mechanism via the CCTSI. They will be consented in private by a CCTSI perinatal nurse or by the study PRA. Women who are within 12 weeks after a delivery can also be referred to us and enrolled in the study. We will post paper flyers advertising the study near OB clinics and we will advertise on the University of Colorado website for clinical trials and the Anschutz Health and Wellness Center website. Women being seen at clinics outside of UCH may have access to flyers about the study, which would encourage them to call the research assistant for more information.

**5.3 Screening and Informed Consent**

Our in-person/telephone screening questions will address the specific inclusion/exclusion criteria for the study. During this screening period, we will only gather information that is directly related to assessing eligibility and suitability for this study. At the beginning of the screening conversation, we will inform potential subjects of the nature and sensitivity of the questions, ask whether this is an appropriate time for them to answer these questions, and tell them this process is expected to take up to 10 minutes. In the interest of confidentiality, we will only record the subject's initials at the beginning of the screening conversation. Then, we will explain to the subject that she will be asked a set of questions to determine eligibility and that at the end, if she appears to be eligible and is interested in pursuing the study, or if she agrees to have her information filed to enable contact for future studies, she will be asked to provide contact/identifying information.

Informed consent will be obtained by one of the physician study staff, the PRA at University of Colorado, or a nurse from the perinatal CCTSI team. During the first two weeks of recruitment, the PRA will be supervised by senior study staff. Subjects who are being consented by non-MDs will routinely be offered the option to speak with one of the physician study staff with any remaining questions or concerns about the study. Although there are non-MDs who may be obtaining consent, physician study staff will be available by pager if needed during the consent process. All subjects will be at least 18 years old and able to provide consent. We will closely follow the guidelines of the COMIRB during interactions with subjects and during procedures for obtaining informed consent. The consent form will be reviewed in detail with each subject and all questions will be answered. Subjects will be given as much time as they want to read, review, and complete the consent form. Subjects who prefer contemplating their decision for days or up to 6 weeks or who wish to discuss their participation in the study with others (family members, friends, and physician) will be encouraged to do so. We will stress that participation in our research study is voluntary, that subjects may withdraw from the study at any time, and that the investigators reserve the right to discontinue the research protocol at any time. A copy of the signed informed consent form will be given to each subject.

**5.4: Eligibility:**

Inclusion Criteria:

1. Age 18-45
2. Postpartum Body Mass Index (BMI): 26-45 kg/m^2^ (≥24 for Asians)

3) Positive history of one or more of the following complications in most recent singleton pregnancy:

- 1. Gestational diabetes mellitus (by Carpenter-Coustan criteria, IADPSG criteria, or a documented clinical diagnosis). Women with a glucose value >200 mg/dL after a 50-g glucose challenge test at >12 weeks gestation will also be included.
  2. Preeclampsia (high blood pressure and proteinuria diagnosed after 20 weeks gestation)
  3. Gestational hypertension (new hypertension diagnosed after 20 weeks without proteinuria)
  4. Pre-term delivery (32-37 weeks)
  5. Small for gestational age (<10th percentile for gestational age)

4) Access to and be willing to use a wi-fi enabled iPhone (5 or higher) or iPod (5 or higher).

5) Capable of providing informed consent

6) Between 4 weeks and 16 weeks after delivery

Exclusion criteria include:

1. Personal history of Type 1 or 2 diabetes
2. Personal history of breast cancer or any other type of cancer other than a basal cell skin cancer;
3. Personal history of major chronic illness all to be assessed by the study physician for ability to participate, including cardiovascular disease (coronary artery disease, congestive heart failure, valvular heart disease, stroke, transient ischemic attack, or intermittent claudication), kidney disease affecting kidney function severe enough to affect participation, liver disease affecting liver function severely enough to affect participation, venous or arterial thromboembolic disease, untreated adrenal insufficiency, depression requiring hospitalization within the past 6 months, or non-pregnancy related illness requiring overnight hospitalization in the past 6 months;
4. Underlying disease/treatment that might interfere with participation in/completion of the study (e.g. significant gastrointestinal conditions, major psychiatric disorders affecting the ability to participate, and others at the discretion of the study clinician);
5. Re-current pregnancy;
6. Pregnancy of twins or multiples;
7. Diagnosis of diseases associated with glucose metabolism;
8. Current or planned participation in a commercial weight loss program (i.e. Jenny Craig) over the duration of the study;
9. Previous or planned bariatric surgery;
10. Taking certain prescription medications including long-term high dose glucocorticoids, atypical antipsychotics associated with weight gain (such as respirdal (respiradone), clozapine (klozaril), olanzapine (zyprexa), quetiapine (seroquel), etc.)) or weight loss medications including prescription (Qsymia, phentermine, topiramate, Belviq, Contrave, Saxenda, Orlistat), or non-prescription (Alli) medications;
11. Taking metformin or other medications known to affect glucose metabolism during the postpartum period;
12. Other active medical problems detected by examination or laboratory testing, at the discretion of the physician;
13. During the first trimester, any fasting blood glucose > 126 mg/dl, any HbA1c at or above 6.5%, or any plasma glucose >200 mg/dl.

**5.5 Treatment assignment and randomization:**

At their first study visit (approximately 6 weeks postpartum), subjects will be randomized into either:

1. Text4Baby Group: 3 study visits (6 weeks, 6 months, 12 months) OR

2. Fit After Baby mHealth Intervention Group: 3 study visits (6 weeks, 6 months, 12 months) AND interaction with the Fit After Baby mHealth program and lifestyle coach

We will randomize in a 2:1 ratio favoring the intervention arm so that we can collect the maximal amount of data from users of the mobile application. This is important because we are collecting data about use of the mobile application in addition to the primary outcome for efficacy. Having more data on actual users will allow us to be more competitive for a future R01 submission emphasizing dissemination and implementation. We have improved the power of the study by adding subjects. Improving the power of the study will increase our likelihood of finding a true difference, which will in turn improve our ability to be competitive for a future R01 application. We will use a computer program to randomize subjects that will generate random treatment assignments using a permuted block scheme with randomly varying block sizes. We will schedule subjects as closely as possible to the 6 week, 6 month, 12 month dates. However, given potential scheduling conflicts with subjects at the clinics, we will allow a window of flexibility of 4-16 weeks postpartum for the 6-week visit. We will also allow one month before and after the 6-month and 12-month visits. After the trial, we will conduct focus groups with participants (2-4 focus groups, 5-8 per group) to assess barriers and facilitators to adoption and engagement of the Fit After Baby program.

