Upon signing the consent form and enrolling in this research study, all women will be scheduled for their first of 3 study visits approximately 6 weeks postpartum. The consent form will include language to allow study staff access to the medical record information to confirm medical diagnoses by the inclusion criteria stated above. Subjects who do not have medical conditions as defined by the inclusion criteria stated above documented in their medical records will not be eligible to continue in the study. If a subject becomes pregnant during the course of the study, she will be asked to be followed during the pregnancy to determine occurrence of pregnancy complications and gestational weight gain.

Study Visits

At study visits, all women will be assessed for clinical outcomes, behavioral outcomes, mediating variables, and moderating variables (see table 3). Clinically relevant labs (pregnancy tests, OGTT, fasting glucose, HbA1c, TSH, LDL, triglycerides) will be reviewed when results are available. All subjects will complete approximately 45 minutes of questionnaires at study visits.

In accordance with ADA recommendations and UCH standard of care guidelines for postpartum diabetes screening for patients with prior GDM, which suggest 6 week postpartum glycemic status check via oral glucose tolerance test (OGTT), all enrolled subjects with a history of GDM will be offered an OGTT. Study staff will schedule this visit and with the subject’s permission, share OGTT results with subject’s pregnancy care provider (MD or CNM), thereby eliminating the scheduling of duplicate lab appointments. We anticipate this collaboration with OB caregivers will be welcomed, as published data demonstrate clinicians have a difficult time getting these women in for their 6 week postpartum OGTT – less than 50% of women had a 6 week postpartum OGTT.^[[42]](#endnote-42)^

All subjects will be instructed to arrive fasting to study visits, i.e. nothing except water for 10 hours prior to study visit. At study visits up to 50 cc of blood will be drawn, including fasting bloods and optional blood for storage.

During the first study visit, all enrolled subjects will be randomized using previously described permuted block scheme to either control or intervention arm.

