Control arm: Subjects who enter the control arm will be shown how to sign up for the free Text4Baby program. Women assigned to the Text4Baby control arm will receive 2-4 free text messages per week from the Text4Baby program,^[[43]](#endnote-43)^ a nonprofit maternal child health program which provides information including baby care and resources for women tailored to their number of weeks postpartum. Since Text4Baby does not emphasize weight loss it will serve as an active control. If women are already enrolled they will be asked to continue to receive texts from the program.

Fit After Baby arm: Women assigned to the Fit After Baby program will use the app (see Table 1 for description of app components), as well as communicate with a lifestyle coach by email or phone. They will receive daily content for 12 weeks, and then less intensive interactions once per week plus home page tracking options until 12 months postpartum. Subjects randomized to the Fit After Baby arm will be shown how to download the app onto their phone. They will also be given a Fitbit and a body weight scale at the 6 week/baseline study visit and shown how to use these.

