**6 months**

6 month visit

**Measures:** Body weight and height: We will determine weight, measured twice wearing light clothing. We will obtain pre-pregnancy weight by self-report. Others have shown a high correlation (R=0.99) between self-reported and clinically measured pre-pregnancy weight.^[[45]](#endnote-45)^ We will measure height and use kg/m^2^ to determine BMI. 2) Demographics: We will collect age, self-reported ethnicity and race, working status, parity, family history of diabetes and cardiovascular disease, prior personal history of pregnancy complications, education level, marital status, number/ages of children living at home, and number of other household members. 3) Pregnancy test: We will obtain urine for rapid determination of hCG at the follow-up visit at 6 and 12 months postpartum. If the test is positive the participant will be referred to her clinician for confirmatory testing. We will not do hCG tests at the baseline visit, since many women will still have positive levels from pregnancy. If a woman is determined to be pregnant during the study year they will be censored at that timepoint. We do not anticipate any harm to participation even if a woman were to become pregnant during the study. 4) Waist Circumference: Per NHANES methodology.^[[46]](#endnote-46)^ 5) Blood pressure: Determined twice, five minutes apart in the seated position after 15 minutes of rest. Values will be averaged. 6) Biomarkers: HbA1c, hsCRP, adiponectin and fasting glucose, insulin, and lipids. 7) Potential mediators: Diet will be assessed by 2005 Block FFQ, administered online during the study visit. Physical activity will be assessed using an adapted Pregnancy Physical Activity Questionnaire (PPAQ).^[[47]](#endnote-47)^ Breastfeeding intensity and frequency will be assessed through a short questionnaire. 8) Potential moderators: Postpartum depression (PPD) will be assessed using the Edinburgh Postnatal Depression Scale (EPDS).^[[48]](#endnote-48)^ Women found to have PPD (defined as an EPDS score ≥12) will be assessed by a study clinician and offered a referral to services. They will be allowed to continue in the study. Any woman screening in for self-harm or harm to others will be immediately referred for mental health evaluation. We will assess appetite and sleep using real-time visual analog scales in the app. 9) Satisfaction: Likert scale for satisfaction and willingness to recommend to a friend.

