**Statistical Analysis**: The analysis for the primary outcomes will be intent-to-treat, using longitudinal mixed methods to account for loss to follow-up and censored participants. Due to the longitudinal nature of this study, we will assess the change in weight from the 6-week study visit to weight at 6 and 12 months by a mixed model analysis with an exchangeable correlation structure and adjustment for weight gain during pregnancy, and breastfeeding (a mediating effect). Within this model, we can further assess differences in weight between various time points by contrasts. We will also compare the delta weight prepregnancy to 6 and 12 months postpartum in the intervention group to the control group using a multivariate regression model, adjusting for age and race. Secondary clinical outcomes will be compared between groups by a generalized linear mixed model analysis, similar to the primary outcome analysis. When necessary, adjustment for multiple comparisons will be made. We will assess reach, effectiveness, and adoption per the RE-AIM model to prepare for a pragmatic trial (Table 2). We will use content-based analysis on focus group data to assess perceived barriers and facilitators to success of the intervention.

**Anticipated results**: Primary outcome: We expect that women who participate in the *Fit After Baby* program will demonstrate increased weight loss in the postpartum year vs. the Text4Baby control group. Secondary outcomes**:** We expect an improvement in cardiometabolic risk factors among women randomized to the Fit After Baby program. We anticipate that increased engagement and satisfaction will be associated with increased weight loss. We expect that decreased caloric intake relative to expenditure and increased physical activity will help to mediate weight loss. We anticipate that postpartum depression may interfere with weight loss as it will decrease engagement with the program, and appetite and sleep may also moderate weight loss.

| **Table 2: Relevant RE-AIM Outcomes** | **Measures/Data Source** | |
| --- | --- | --- |
| **REACH** | | |
| 1) Proportion of approached women agreeing to participate  2) Proportion of recruited women initiating program | | 1) Recruitment data  2) App usage data |
| **EFFECTIVENESS** | | |

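### Baseline may fall at 4 to 16 weeks postpartum while follow-up is counted from delivery, so the baseline-to-6-month interval runs from about 6 to 26 weeks, and the stated model has no timing term

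*Protocol*

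**What the plan says.** **Baseline.** Section 5.4 requires women to be "Between 4 weeks and 16 weeks after delivery". Section 5.5 aims at about 6 weeks, but "we will allow a window of flexibility of 4-16 weeks postpartum for the 6-week visit". Section 5.6 adds: "During the first study visit, all enrolled subjects will be randomized". Women in the intervention arm are shown how to download the app and are given their devices at this same visit.

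**Follow-up.** The Measures paragraph places the pregnancy test "at the follow-up visit at 6 and 12 months postpartum", and Table 3 heads Visits 2 and 3 in months postpartum. The clock therefore starts at delivery. Section 5.5 gives the tolerance: "We will also allow one month before and after the 6-month and 12-month visits".

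**Programme.** Of the Fit After Baby arm, section 5.6 says "They will receive daily content for 12 weeks". Contact then drops to once a week until 12 months postpartum.

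**Outcome and model.** Change in weight from baseline to 6 months and to one year is among the primary outcomes (section 5.6, Study Outcomes). Under Statistical Analysis, "we will assess the change in weight from the 6-week study visit to weight at 6 and 12 months" by a mixed model. The covariates named are weight gain during pregnancy and breastfeeding. Neither weeks postpartum at baseline nor elapsed time is listed.

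**Enrolment wording.** Section 5.2 says: "Women who are within 12 weeks after a delivery can also be referred to us and enrolled in the study".

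**The concern.** The start of the interval can move by 12 weeks while its end is tied to delivery. Two women who both contribute a 6-month change may therefore have been observed, and exposed to the programme, for very different lengths of time. Some will be weighed before the intensive phase of the programme has finished. Baseline weights taken at different points after delivery may also differ for reasons unrelated to treatment. The model as written does not account for this.

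What is at stake is mainly the 6-month contrast. It would average partial and completed exposure, and it would carry noise that a known pre-randomisation variable could remove. The trial is a pilot meant to inform a larger one (section 5.1), so a 6-month effect at undefined exposure is a weak design input.

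**Working it through.** **Inputs from the protocol.** Baseline at 4-16 weeks, nominal 6 (sections 5.4, 5.5). Visits at 6 and 12 months from delivery, ±1 month (section 5.5, Table 3). Daily content for 12 weeks (section 5.6). 54 versus 27 women, difference 4.2 kg, SD 5.7 kg, power at least 87% for 12-month change (power paragraph). Conversion: 1 month = 365.25/12/7 = 4.348 weeks.

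**1. The stated power.** A two-sample t-test with 79 df, taking two-sided alpha 0.05 (not stated, so assumed), gives 87.0%. The normal approximation gives 87.8%. The protocol's figure is reproduced.

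**2. Interval from baseline to follow-up.** Shortest = earliest visit − 16 weeks. Longest = latest visit − 4 weeks.

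| Visit | Window (weeks) | Shortest | Nominal | Longest | Ratio |
|---|---|---|---|---|---|
| 6 months | 21.7-30.4 | 21.7 − 16 = 5.7 | 26.1 − 6 = 20.1 | 30.4 − 4 = 26.4 | 4.6 |
| 12 months | 47.8-56.5 | 47.8 − 16 = 31.8 | 52.2 − 6 = 46.2 | 56.5 − 4 = 52.5 | 1.65 |

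Counting 6 months as 26 weeks and one month as 4 weeks gives 6 to 26 weeks, so the result does not depend on the convention.

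**3. Programme received by the 6-month visit.** With baseline at week 16:
- earliest visit: 21.7 − 16 = 5.7 weeks
- on-time visit: 26.1 − 16 = 10.1 weeks
- latest visit: 30.4 − 16 = 14.4 weeks

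An on-time visit precedes the end of the 12 weeks when baseline is later than 26.1 − 12 = week 14.1. The earliest permitted visit does so when baseline is later than 21.7 − 12 = week 9.7. A woman with baseline at week 6 has had at least 21.7 − 6 = 15.7 weeks.

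**4. How many women.** Assume baselines uniform over 4-16 weeks.
- All visits on time: (16 − 14.1)/12 = about 16%.
- Visits uniform over ±1 month: the short-exposure region is a triangle of side 28.0 − 21.74 = 6.26 weeks, so (6.26²/2)/(8.70 × 12) = 18.8%.

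**5. Chance imbalance.** The SD of a uniform 12-week spread is 12/√12 = 3.46 weeks. The standard error of the difference between arms is 3.46 × √(1/54 + 1/27) = 0.82 weeks, giving 95% limits of ±1.6 weeks. At assumed weight slopes of 0.1-0.3 kg/week this is 0.16-0.48 kg. For comparison, the ordinary sampling error of the contrast is 5.7 × √(1/54 + 1/27) = 1.34 kg, or ±2.6 kg.

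**6. Effect on 12-month power.** Interval variance = 12 + 8.70²/12 = 18.3 weeks². With slope b, SD = √(5.7² + 18.3b²), assuming none of this spread is already in the 5.7 kg.

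| b (kg/week) | SD (kg) | Power (t) |
|---|---|---|
| 0.1 | 5.72 | 86.8% |
| 0.2 | 5.76 | 86.3% |
| 0.3 | 5.84 | 85.4% |

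**The case against.** Counting from delivery is a defensible choice, because the background section frames the problem as weight kept beyond 6-12 months postpartum. Section 5.5 also aims for visits near the nominal dates and presents the windows as room for scheduling conflicts. That makes a uniform spread, whose mean is 10 weeks, pessimistic. This stands. Late baselines are still not only slips, since 16 weeks is an eligibility limit and a woman referred at week 12 cannot have a 6-week baseline.

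Four stronger readings are tempting, and the documents do not support them.

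- *Half the women are measured before the daily content ends.* The share (16 − 9.7)/12 = 52% requires every 6-month visit to be a full month early as well as uniform baselines.
- *The comparison is biased.* Randomisation takes place at the baseline visit, so timing balances in expectation. The 0.16-0.48 kg is the 95% limit of a chance imbalance at an assumed slope, and it is small beside ±2.6 kg.
- *The power claim fails.* Power is stated for 12 months, when the daily phase is always over, and it falls by at most about 1.6 points.
- *The enrolment limits contradict each other.* Section 5.2 can be read as limiting referral and enrolment, with the first visit allowed up to week 16. The loose labels left from the flow diagram cannot be read as an enrolment limit.

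Two further limits hold. The primary outcome measured from pre-pregnancy weight does not use baseline weight, although exposure still varies. Weekly contact continues after the daily phase, so what may be incomplete at 6 months is the daily content only.

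A separate SAP could specify actual visit times, and the 6-week visit may be only a label. But the protocol itself names the covariates, and timing is not among them.

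**Conclusion.** The point holds as a matter of precision and definition. The windows allow a 4.6-fold range in the interval behind the 6-month change, and even an on-time 6-month visit can precede the end of the daily content. That second result rests on the 16-week limit. If baseline had to fall by week 12, an on-time visit would come 26.1 − 12 = 14.1 weeks after baseline, and only an early visit (21.7 − 12 = 9.7 weeks) would fall short.

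The share affected, about 16-19%, rests on uniform enrolment and is probably too high. The dilution of the 6-month effect cannot be put in kilograms from the documents. At 12 months the consequence is minor. The change is worth making because it is almost free, not because the trial's main conclusion is threatened.

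**What to change.** 1. **Model.** Under Statistical Analysis, add weeks postpartum at baseline, with its interaction with visit, to the primary mixed model. It is fixed before randomisation and can be computed from the delivery and visit dates that eligibility and scheduling already require. The cost is one or two degrees of freedom when the 6- and 12-month changes are the responses. If baseline weight is also modelled as a response, the interaction is essential, because a main effect alone would cancel out of the change, and it takes one more degree of freedom.

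2. **Optional scheduling preference.** Within the existing 5-7 month window, and equally in both arms, place late enrollers' 6-month visit at 12 weeks or more after randomisation where feasible. This always fits, since 16 + 12 = 28 weeks is before 30.4 weeks. It should not be a hard rule: at the extreme it leaves 30.4 − 28 = 2.4 weeks instead of 8.7, which risks missing weights.

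3. **Wording.** State whether the 12 weeks in section 5.2 limits referral and enrolment only, so that it reads consistently with the 16 weeks in sections 5.4 and 5.5. This costs one sentence.
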